### Randomization and allocation concealment

If found to meet the inclusion criteria participants will be randomized directly after baseline assessment to the telerehabilitation group or to the control group. A web-based random sequence generator without limiting conditions will generate the randomization sequence. The randomization sequence list will be created in advance of recruitment by an experienced scientist who is not a member of the research team. Group allocation will be obtained by phone (once baseline data has been collected and recorded) from a member of staff who is not involved in the study at the outpatient clinic at Sunnaas Rehabilitation Hospital. Once the participant has been randomized, the research investigator will inform which group they have been allocated to. If the patient is included in the intervention group, further arrangement for the installation of the telerehabilitation equipment and training in the use of the computer will be addressed. The participant, relatives and/or caregivers will be given careful instructions on how to preserve allocation concealment in the 4-week control and follow-up testing, including instructions not to discuss treatment with the blinded SLPs.

### Blinding

Neither the participant nor the SLPs performing the therapy are blinded to treatment allocation due to the nature of the intervention. However, baseline assessment will be blinded as it will be performed before group allocation. The 4-week control and follow-up testing will be performed by external SLPs blinded to group allocation. All data collection sessions will be audio and video taped. In cases where allocation is inadvertently revealed by the patient, relatives and/or caregivers during conversation or by other means, a second SLP blinded to treatment allocation will re-score the test session using the recorded video tape.

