### Screening for eligibility, baseline assessment and recruitment

Detailed information about the project will be provided and the research investigator will seek informed consent before carrying out baseline testing. The Informed Consent Form and Information Sheet are accessible for people with aphasia. Relatives and caretakers will be carefully informed about participation. Eligibility will be established by an ambulatory visit ([name], [name]) to the stroke unit, patient’s home or rehabilitation institution. Their eligibility will be confirmed by using clinical observations, medical information and language tests. The baseline assessment consists of the NGA subtests and the Verb and Sentence Test (VAST) subtest sentence production. If the potential participant is excluded, an explanation that the project is not suitable for the patient will be given. The number of those screened, but not included after screening, will be recorded along with the reason for exclusion. When included in the project, the participant’s demographic data will be collected including age, gender, relationship status and housing conditions. Relevant medical data, time post onset of stroke and type and location of stroke will be charted. The Modified Rankin Scale will describe the functional status of the patients, and be registered at each assessment time point (baseline, 4 weeks and 4 months; Fig. 1). Participants will be contacted up to three times for participation in outcome and follow-up assessment. No further data will be collected for those who discontinue study participation.

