## Sample size

No large RCTs have been carried out within the field of aphasia telerehabilitation, especially with the use of videoconference SLT. Previous studies have used interventions not applicable with the current protocol, and have been of varying quality and used small sample sizes. We were, therefore, unable to calculate an a prior accurate sample size. Thus, our pilot RCT will support a more accurate sample size estimate and to inform a definitive trial of the effect of intensive telerehabilitation for aphasia. We will investigate possible effects using the percentile score of the NGA naming subtest where we consider the minimal clinically meaningful effect to be an improvement of 8 percentile scores. Given a standard deviation of 18.17 (based on recently collected data from another project without telerehabilitation), 32 participants will be sufficient to detect a significant improvement within a group between time points using a pairwise comparison, with a significance level of 5 and a power of 80. This will enable the study to make some suggestions on effectivity. Considering possible dropouts, the study aims to include 40 participants in each group, with a total number of 80 subjects. We anticipate that results from this pilot RCT will yield data to inform a more accurate sample size calculation for future definitive RCTs.

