## Statistical analysis

Data will be analyzed on an intention-to-treat basis. Descriptive statistics will be applied and the characteristics of the sample will be described. The trial is a longitudinal study with continuous repeated measurements. The data will be analyzed by using mixed models. A mixed model is preferred to the more traditional repeated measures analysis of variance (ANOVA) because of its advantages in the way in which it accommodates missing values. Data will be examined for differences over time and between groups. Subgroup analysis will be performed to explore factors considered to affect the outcome of the trial like differences in time since onset of stroke or demographic and stroke-related factors. Qualitative data collected from semi-structured interviews will be suitably coded for qualitative responses to be categorized and examined.

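### The type of tester changes between baseline and first follow-up in both arms, so the within-group improvement on which the trial is sized cannot support a statement about effectiveness; the randomised contrast is not biased by this

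*Protocol article*

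**What the plan says.** Two sections of the protocol article settle who tests when. Under Screening for eligibility, baseline assessment and recruitment, "the research investigator will seek informed consent before carrying out baseline testing", and "The baseline assessment consists of the NGA subtests and the Verb and Sentence Test (VAST) subtest sentence production". The naming subtest that decides eligibility is thus part of that baseline session. Under Blinding, "baseline assessment will be blinded as it will be performed before group allocation", whereas "The 4-week control and follow-up testing will be performed by external SLPs blinded to group allocation". The same section adds that "All data collection sessions will be audio and video taped". Re-scoring from tape is described for one situation only, where allocation has been revealed.

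The Sample size section takes 8 percentile points as the smallest meaningful improvement and an SD of 18.17 from another project. It states that 32 participants are "sufficient to detect a significant improvement within a group between time points using a pairwise comparison", and expects this to let the study say something about effectiveness. The Statistical analysis section plans mixed models and states: "Data will be examined for differences over time and between groups".

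**The concern.** Between baseline and 4 weeks, two things change for everyone: time passes, and the tester goes from the research investigator to an external speech-language pathologist. If the two groups of testers differ systematically in cueing, time allowed or the crediting of near-correct responses, that difference enters the change score at full size. No analysis of the within-group data can remove it, because no participant has the same type of tester at baseline and at follow-up.

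Within-group change is the quantity behind the stated 32 per group. A tester difference could produce an apparent improvement in both arms or hide a real one. It adds to sources of uncontrolled change that would be present with one tester throughout: natural recovery in a sample recruited at any time after stroke, usual care, practice on the test, and regression to the mean after entry is limited to the 70th percentile or below.

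**Working it through.** **Inputs.** From the Sample size section: improvement 8 points, SD 18.17, significance level 5%, power 80%, 32 participants for the paired comparison, 40 enrolled per group. Not stated: whether the test is one- or two-sided, and whether 18.17 is the SD of change or of a single score. I take it as the SD of change. The size of any tester shift is not in the documents, so the shifts below are assumptions.

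**Step 1: reproduce the plan's figure.** Paired normal approximation, n = [SD × (z_alpha + z_power) / difference]².
- One-sided 5%: [18.17 × (1.645 + 0.842) / 8]² = 31.9, rounded up to 32.
- Two-sided 5%: [18.17 × (1.960 + 0.842) / 8]² = 40.5, rounded up to 41.

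The stated 32 is recovered as a one-sided paired calculation. This confirms that the sizing rests on change within a group.

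**Step 2: precision of the mean change.** SE = 18.17 / √32 = 3.21 points.

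**Step 3: effect of a tester shift when there is no true change.** With z = shift / 3.21, the two-sided rejection rate is 1 − Φ(1.96 − z) + Φ(−1.96 − z).

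| Assumed shift (points) | z | Rejection rate, normal | Rejection rate, noncentral t |
|---|---|---|---|
| 0 | 0 | 5.0% | 5.0% |
| 2 | 0.623 | 0.0906 + 0.0049 = 9.5% | 9.3% |
| 3 | 0.934 | 0.1525 + 0.0019 = 15.4% | 14.8% |
| 5 | 1.557 | 0.3434 + 0.0002 = 34.4% | 32.6% |

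With the one-sided test that reproduces 32, an upward shift of 2 points gives 15.0% and one of 4 points gives 33.5% (noncentral t).

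**Step 4: a shift in the other direction.** With a true improvement of 8 points and n = 32, a shift of −2 points lowers power from 78.5% to 57.2% one-sided, or from 67.5% to 44.0% two-sided (noncentral t).

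**Step 5: the randomised contrast.** Let s be a shift common to both arms. The difference in mean change is (change in telerehabilitation + s) − (change in control + s), so s drops out. A simulation agrees: with no true difference, 40 per arm and a common shift of 4 points, the mean estimated difference was −0.09 and the two-sided rejection rate 5.2% over 4,000 runs.

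**Step 6: the interval from 4 weeks to 4 months.** External testers perform both assessments, so this switch of tester does not affect change over that interval.

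**The case against.** The strongest reply is that the trial's question is comparative. The stated aim is better naming than with usual care, the abstract promises between-group comparisons by intention to treat, and a pre-allocation baseline followed by blinded external assessment is a defensible design. All of that stands: the primary comparison is not biased by a shift common to both arms.

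It is also fair that no shift is demonstrated. The article gives no inter-rater figure for the naming subtest, and tester training and scoring rules may stand in the full protocol. Within-group change would be weak evidence of effect even with one tester throughout. These points limit the weight of the concern but do not remove it, because the article itself fixes both the change of tester and the within-group comparison as the basis of its sizing.

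A reader might infer more than the documents support:
- **That the plan itself treats scoring as dependent on the tester.** The instruction that "a second SLP blinded to treatment allocation will re-score the test session using the recorded video tape" applies only when allocation has been revealed. It guards against knowledge of the arm and says nothing about differences between blinded testers.
- **That the entry limit makes the tester change favour improvement.** The limit produces regression to the mean whoever does the testing. Nothing suggests that baseline scores are set low in order to enrol.
- **That the sizing of the definitive trial would be misled.** A constant shift in both arms alters neither the between-group difference nor the SD that a comparative trial would use.

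**Conclusion.** The point holds in a limited form and is minor. From baseline to either follow-up, type of tester and time are fully aliased in both arms. The randomised between-group contrast is unaffected by a common shift; the within-group improvement behind the stated 32 per group is exposed.

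A shift of 2 to 5 points would take the two-sided 5% paired test to a false-positive rate of about 10% to 34%. That range rests on an assumed shift, on 18.17 being the SD of change, and on 32 analysed participants. It shows how sensitive the paired test is and is not an estimate of bias in this trial.

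One fact rests on reading the text: the baseline tester is identified from the sentence that has the investigator obtain consent before testing, and from the contrast with external testers later. The article has no separate statement on it.

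**What to change.** Amend the Sample size and Statistical analysis sections so that all statements about effectiveness rest on the between-group contrast at 4 weeks and 4 months. Report change from baseline within a group as descriptive only, and note beside it that the type of tester changed after baseline.

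This costs wording only: no visit, procedure or additional scoring. The real cost is in what the trial can claim. The stated 32 per group refers to the within-group comparison, so the trial gives up its only powered claim. For scale, if 18.17 is also the SD of the outcome compared between arms, a two-sided 5% test of an 8-point difference with 40 per arm has SE = 18.17 × √(2/40) = 4.06 and power Φ(8/4.06 − 1.96), about 50%. With 32 per arm it is about 42%. The Discussion already concedes that the trial falls short of the sample size its power assumptions require, so the amendment brings the sizing text into line with that.

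Having the external testers re-score the baseline tapes may seem an obvious alternative, but I would not recommend it. Baseline would then be scored from tape and follow-up mainly in the session, so mode of scoring would be aliased with time instead. Tape scoring also cannot undo differences in how the test was administered, and it needs extra scoring time.

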## Outcome measures

### Primary endpoint

The primary endpoint of this study is naming ability 4 month post randomization, measured by the subtest “naming” in the NGA. The minimum difference of 8 percentile score is considered clinically significant. For the assessment of language functioning, the NGA [27] with the subtests comprehension, naming and repetition is included in the test battery. Percentile scores (i.e., percentile rank compared to the norm material of the NGA) will be used because they – for all severity levels of aphasia – mirror clinically relevant progression more accurately than raw scores.

### Key secondary endpoint(s)

Key secondary endpoints are other language functions 4 months post randomization measured by the NGA subtest “comprehension” and “repetition.” In addition, the VAST subtest sentence production [28], assesses the ability of verb and sentence production beyond words. Functional communication is assessed using the Communicative Effectiveness Index (CETI) [29]. These endpoints are scored/collected immediately after the intervention (4 weeks) and at the 4-month post randomization follow-up to detect any extended effect of the intervention.

### Other secondary endpoints

Quality of life will be assessed by using the Stroke and Aphasia Quality of Life scale (SAQOL-39) [30]. The SAQOL-39 is a quality of life scale developed specifically with regard to persons with aphasia. In addition, the experiences of patients, relatives and therapists with the telerehabilitation services and their participation within the trial will be gathered using questionnaires and semi-structured interviews with both SLPs and selected participants. Adverse events, including technical challenges, will be logged.

## Intervention

### Control group (usual care)

The control group will receive usual care provided by SLPs at the community level or in rehabilitation institutions. As usual care varies in the different municipalities and institutions, both in terms of type and frequency, the services provided for each participant will depend on the local resources available. The therapy may include face-to-face SLT in a single session or by group. The dose of therapy received from inclusion to follow-up 4 months post randomization will be recorded. Participants who are randomized to the control group will not receive any project specific intervention, but will, at the 4-month post-randomization follow-up, i.e., after their study participation, be referred for participation in an intensive language training program at Sunnaas Rehabilitation Hospital.

### Telerehabilitation group

As current scientific evidence favors intensity in aphasia interventions, our trial will offer a high-intensity therapy. Because there still is uncertainty about the best therapy approach within aphasia rehabilitation, no specific approach or theory has been chosen for our intervention beyond tasks that can enhance functional expressive communication. In the intervention group, the participants will receive augmented language training of 5 h a week over four consecutive weeks. This will be in addition to any usual SLT the participant is already receiving. The aim is to give 1 h SLT via videoconference per day, 5 days per week, but this can be adjusted to the participant’s timetable and rehabilitation schedule if necessary. Participants with ≥ 16 sessions over 32 days are considered to be per protocol. The SLT will be performed by an SLP using videoconference via the Internet from Sunnaas Rehabilitation Hospital to the laptop in the patient’s home, or rehabilitation/nursing ward. To secure treatment fidelity and replication for future studies and transparency of reporting, we have used the Template for intervention Description and Replication (TIDieR) Checklist and Guide (Additional file 3 [31]), to record and describe the intervention delivered by videoconference. The main features of the intervention using TIDier are illustrated in Table 1.

**Table 1 Tab1:** The intervention illustrated by main features from the Template for intervention Description and Replication (TIDieR) Checklist and Guide

*Brief name:* Intensive speech and language therapy by videoconference	
*Why:* To improve expressive language function in patients with aphasia after stroke	
*What:* Intensive speech and language therapy with an emphasis on naming. The therapy will be tailored to the participant’s language impairment level and focus on expressive language and everyday communication. Material used in the training will include the Newcastle University Aphasia Therapy Resources (NUMA), a collection of SLP-made tasks for aphasia compiled as *Sareptas afasikrukke* and Lexia (computer-based training program). In addition, text and pictures from the Internet may also be used	
*Who provided:* Speech and language pathologists sited at Sunnaas Rehabilitation Hospital. Speech-language pathologists (SLPs) will receive training in how to give intervention by videoconference within the context of a clinical trial	
*How:* Using videoconference and remote control software to a laptop at the patient’s location	
*Where:* From Sunnaas Rehabilitation Hospital to the patient’s home or institution, e.g., rehabilitation ward or nursing home	
*When/How much:* The experimental intervention consists of 5 h of speech and language therapy a week, over 4 weeks (total dose of 20 h of therapy). Participants with ≥ 16 sessions over 32 days will be considered to be per protocol	

The SLT delivered by videoconference will be tailored to the participant’s language impairment. We will work on all language modalities; however, the intervention will have an emphasis on oral naming and speech production. As the therapy will be individualized, there will be a broad range of tasks including word production in “natural” sequences (e.g., weekdays and months), picture naming, discussion about familiar topics (e.g., hobbies and family) and conversations about a concrete subject, picture or situation. Since the main focus is expressive speech, material stimulating everyday communication will be the first choice and this will be tailored to the individual participant’s needs and goals. Material used in the intervention includes Norwegian versions of the Newcastle University Aphasia Therapy Resources (NUMA) [32–34], a collection of SLP-made tasks for aphasia compiled as *Sareptas afasikrukke* [35] and for some patients Lexia, a computer-based training program. In addition, text and pictures from the Internet, such as the easy to read newspaper *Klar Tale*, may be used if applicable. The SLPs in our trial will receive training in how to use the chosen material within the context of a clinical trial and computer software to provide the intervention by videoconference.

The broad range of material accessible to the intervention gives the therapist an optimal setting to tailor the therapy to the patient’s impairment level. The therapy will be in line with patient’s own goals, where a personalization of the therapy is considered a key of success with regards to compliance to protocol. Because the patients continue to receive ongoing care, we expect a wide range of variation of usual care with regards to type of therapy and the intensity with which it is given. Usual care will reflect upon rehabilitation resources available. To account for this expected heterogeneity, careful record of the usual care provided and accessed will be completed for all participants.

### Fidelity

For each participant in the intervention group, a report will be written. The report will describe the tailored therapy that each participant has received via videoconference. The content of the reports will be compared through regular fidelity reviews with the intervention description in the trial protocol.

## Technical solutions

As already tested in our feasibility study [24], we will use videoconference software and equipment installed at Sunnaas Rehabilitation Hospital and in study laptops given to the participants. The videoconference software is delivered by the “Norwegian Health Net (NHN),” a company owned by the Ministry of Health and Care services. Videoconference is provided through encrypted software which meets requirements with regards to data safety aspects, privacy and confidentiality. As the therapy sessions are live, there are no recordings or storage of video, sound or picture. The software we will use for the videoconference is Cisco Jabber/ Acano. In addition, the SLPs will also use the software called LogMeIn which allows the therapist to remotely control the participant’s computer, and has been shown to be a valuable tool in delivering therapy and assistance should technical problems arise [24].

Our current technical setup builds upon experience from the feasibility study “Language training straight home” [24]. In this former feasibility study some areas for improvement were identified which have been integrated in the present protocol. To maintain safety aspects a checklist has been implemented to be used at the start of each therapy session to control and adjust the patient’s physical environment. This is to ensure optimal training conditions, preserve accurate procedures in case of emergency and to accommodate privacy issues. When it comes to the technical aspects of delivering aphasia rehabilitation by videoconference, one expects to encounter technical challenges not revealed during the small feasibility study (*n* = 4). A separate log to map technical error has been developed and integrated into the protocol. Furthermore, the technical solutions tested in the feasibility study have been improved compared to the original technical setup. This includes a separate speaker to improve sound quality and a wide-angle web camera to enable the therapist to see the patient’s upper body in case alternative communication approaches, such as the use of body language and/or gestures, are needed.

